**Methods:**

Obj.1: The costs incurred by participants in the two groups during their ED visit will be calculated using the Time-Driven Activity-Based Costing (TDABC) method. These costs will be compared using generalized linear models. Obj. 2: The ICER of the two models will be evaluated over three months via a cost-utility analysis that will combine costs and effectiveness data (quality-adjusted life years) using both Health system and Societal perspectives (patient + health system costs). Obj. 3: The 2-year ICER of the three above-mentioned models will be estimated using a mathematical model including a decision tree (0–3 months post-visit) and a Markov model (3–24 months post-visit), also using both Health system and Societal perspectives. Data to answer the three objectives will come from data collected during a randomized clinical trial (n = 78, CHU de Québec)which will be supplemented with data obtained via some of the CHU de Québec administrative databases (nominative data; SIURGE (ED management software), Cristal-Net (patient electronic record), and the ED’s pharmacy transactions directory; administrative data: drug costs repository), the literature, and public cost repositories.

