As part of the cost-utility analysis (Objective 2) and hybrid mathematical model (Objective 3), the efficiency of the ED models of care will be assessed using an incremental cost-effectiveness ratio (ICER). The resulting ICER will be reported in terms of incremental cost per quality-adjusted life years (QALY) gained, between the models of care. The follow-up costs of each participant recorded via the self-administered follow-up questionnaires completed at 1 and 3 months during the pilot pragmatic RCT will be added to the distribution of ED visit costs for each individual obtained under Objective 1. Once all costs have been added, an average will be calculated to obtain an average cost per participant at 3 months, for each model of care (Objective 2 & 3 –decision tree). The questionnaires provided data on resources used by each participant during follow-up such as ED re-visits for the same condition, number of consultations with other health professionals in the public and private sector, imaging tests used, etc. The costs of all resources used in the public healthcare system will be drawn from public cost repositories data from the *Régie de l’assurance-maladie du Québec* (RAMQ) (costs related to the emergency physician and other physicians consulted, drugs, laboratory analysis, imaging tests) [47]. Hourly rates for the primary contact physiotherapist and other health professionals consulted (e.g., massage therapist, chiropractor, osteopath) will be derived from a search of the grey literature and will be based on rates in effect within the private healthcare system, since the majority of these professionals work within this system [47]. Costs related to the use of technical aids (e.g., cane, crutches, walker) will also come from a grey literature search. It should be noted that the salary data available from human resources for all healthcare professionals (physicians and allied health professionals) considered will not allow for variability in hourly costs. The only source of variability considered for the purpose of these analyses will be that related to the time required for ED processes. Utility scores were obtained at the initial visit [48] and at 1 and 3 months using the EQ-5D-5L, a generic standardized questionnaire designed to measure health status in an economic and clinical evaluation [49]. The EQ-5D-5L has been found to be reliable, valid, and sensitive to change [50, 51]. The difference in utility scores between the 3-month follow-up and baseline will be calculated for each participant using area-under-the-curve analyses. Once the difference in utility scores will be calculated for each participant, the differences will be averaged to obtain the average gain or loss in utility scores per ED care model. The mean gain or loss in utility scores will then be transformed into QALYs. The efficiency values and the costs from 3 to 24 months required to run the Markov model (Objective 3) for the three models of care will be taken from the literature.

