**Fig 3 pone.0277369.g004:**
[figure not shown]
Projected Markov model covering the period from three to 24 months post initial ED visit.

Both the cost-utility analysis (Objective 2) and the hybrid mathematical model (Objective 3) will be conducted from a Health system and a Societal perspective. Results obtained via the EQ-5D-5L at 1 and 3 months (Objective 2 & 3 –decision tree) will be converted to utility scores using the Canadian conversion algorithm developed by Xie et al. [54]. As the 3-month retention rate for the pilot pragmatic trial was 80% [29], some participants’ data are missing (service and resource use, costs, utility scores). Missing data will be imputed using the Missing not at random (MNAR) multiple imputation method [55]. Patient characteristics believed to have influenced loss to follow-up at 1 and 3 months (e.g., socioeconomic status; level of pain and level of catastrophizing at the ED visit) will be examined to identify if they are indeed predictors of loss to follow-up. Characteristics shown to influence follow-up will be used within multiple imputations and within sensitivity analyses regarding these variables. Uncertainty in cost and effectiveness measures for the cost-utility analysis (Objective 2) will be obtained using non-parametric bootstrap resampling with replacement. Uncertainty in the hybrid model parameters (probabilities, costs, and efficiency) (Objective 3) will be obtained via a probabilistic sensitivity analysis performed using a Monte Carlo simulation. Three scenarios will be considered in the probabilistic sensitivity analyses. The first will assume that all participants with missing follow-up data in the control group will have utility scores at 3 months corresponding to those of the 95th percentile, while all those missing in the intervention group will have scores corresponding to those of the 5th percentile. For the second scenario, we will re-analyze all parameters included in the model, excluding outliers. Finally, in the third and last scenario, the different states of the Markov Model will be based not on the level of pain, but on the level of interference of pain on daily activities. Both uncertainties will be represented visually using a cost-effectiveness diagram, cost-effectiveness acceptability curve, and cost-effectiveness acceptability frontier [35]. As there are significant differences between men and women in the strategies used to cope with pain, and the use of health system services and resources during a painful episode (e.g., [56, 57]), subgroup analyses of men and women will be performed for both objectives (p < .05). Subgroup analyses will also be performed according to MSKD category (spine, upper extremity, and lower extremity) for both objectives (p < .05). All the statistical analyses carried out as part of this project and their detailed reporting in scientific publications will adhere to the CHEERS 2022 standard [58].

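### Follow-up allied-health visits in the public sector fall under two conflicting price rules, and one of them puts a private price into the Health system ICER

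*Protocol article*

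**What the plan says.** All the pricing text is in the protocol article under Study outcomes.

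- **Resource data.** The 1- and 3-month questionnaires gave, among other items, the "number of consultations with other health professionals in the public and private sector".
- **Rule A, public prices.** "The costs of all resources used in the public healthcare system will be drawn from public cost repositories data", namely the provincial health insurer's. The bracketed items are "costs related to the emergency physician and other physicians consulted, drugs, laboratory analysis, imaging tests".
- **Rule B, private prices.** "Hourly rates for the primary contact physiotherapist and other health professionals consulted" are to be sought in grey-literature sources; they "will be based on rates in effect within the private healthcare system, since the majority of these professionals work within this system". The examples given are massage therapist, chiropractor and osteopath.

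The resulting follow-up costs are added to each participant's ED visit cost. They are then averaged into a 3-month cost per model of care, which feeds Objective 2 and the decision tree of Objective 3. Under Data analysis and interpretation of results, both analyses "will be conducted from a Health system and a Societal perspective". The abstract defines the Societal perspective as patient costs plus health system costs.

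**The concern.** A public-sector physiotherapy visit after discharge is a resource used in the public system, so Rule A asks for a public price. It is also a consultation with one of the professionals named in Rule B, which asks for a private rate and makes no exception by sector. The reason given for Rule B, that most of these professionals work privately, concedes that some do not, and the questionnaire counts visits to those who do not.

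The conflict matters most for the Health system perspective. If privately paid visits are borne by the patient, the allied-health visits left in that perspective are the public ones. Those are the visits for which a private rate is not the payer's cost. Because the Societal perspective includes health system costs, any mispricing carries into it too. Allied-health follow-up is also a resource that could plausibly differ between a pathway with a physiotherapist and one without, in which case the error would not cancel between arms.

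The planned uncertainty analyses would not clearly expose the problem. For these costs the article allows variability only in how long ED processes take. The Objective 2 bootstrap resamples participants and leaves a fixed unit price unchanged. The Objective 3 probabilistic analysis does vary costs, but spread around a wrongly centred price does not correct the centre. None of the three named scenarios (extreme utilities for missing data, exclusion of outliers, Markov states by pain interference) changes the price by sector.

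**Working it through.** The article gives no unit cost, visit count or ICER on this point, so there is no figure to reproduce. The check is a reading of the two rules, followed by a formula for the error.

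**Step 1: which rule covers which visit**

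| Follow-up resource | Rule A (public repositories) | Rule B (private rates) |
|---|---|---|
| Physician, drug, laboratory, imaging (public) | Yes, listed | No |
| Allied-health visit, private sector | No | Yes |
| Allied-health visit, public sector | Yes by the general wording, but not listed | Yes, no exception by sector |

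Only the last row is in conflict. An analyst following Rule A finds no allied-health item in its list. An analyst following Rule B applies a private rate to a public visit.

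**Step 2: the error if Rule B is applied to public visits**

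Let u be the public unit cost of one visit, k the private price of the same visit divided by u, Δv the between-arm difference in mean public allied-health visits per participant, and ΔQ the between-arm difference in mean QALYs.

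- Error per public visit = u × (k − 1)
- Error in incremental cost = Δv × u × (k − 1)
- Shift in the ICER = Δv × u × (k − 1) / ΔQ

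The error is zero if k = 1 or Δv = 0. Its sign follows the signs of Δv and (k − 1), and neither is given.

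**Step 3: illustration on assumed values**

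Assumed ranges: k from 1.0 to 2.0, Δv from 0.1 to 1, ΔQ from 0.005 to 0.02 over three months. None of these comes from the documents. Shifts are in multiples of u per QALY.

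| Δv | k | ΔQ | Δv × (k − 1) / ΔQ |
|---|---|---|---|
| any | 1.0 | any | 0 |
| 0.1 | 1.5 | 0.02 | 0.1 × 0.5 / 0.02 = 2.5 |
| 0.5 | 1.5 | 0.02 | 0.5 × 0.5 / 0.02 = 12.5 |
| 0.5 | 1.5 | 0.005 | 0.5 × 0.5 / 0.005 = 50 |
| 1.0 | 2.0 | 0.005 | 1.0 × 1.0 / 0.005 = 200 |

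In money, take an assumed private fee of $80 to $100 and a public unit cost between 50% and 100% of it. The error per public visit then runs from (1 − 1.0) × $80 = $0 to (1 − 0.5) × $100 = $50. At the upper corner u = $50, so the ICER shift is 200 × $50 = $10,000 per QALY. That corner combines the largest value of every assumption. It shows that a small QALY denominator can magnify a modest price error; it is not an estimate.

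**The case against.** The strongest reply is that the two sentences can be read together: public use takes public prices as a general rule, and mainly private professions take private rates. The examples under Rule B are professions of that kind. On this reading the bracketed list in Rule A is only illustrative, and the plan needs one clarifying sentence. It can be added that one price source per profession is a disclosed and referenced simplification, that it touches a minority of visits if most are private, and that no material effect on the ICER has been shown.

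Part of this stands. The text does not unambiguously fix a private price for public visits, and the size is unknown. But the reconciling reading has to add a sector exception that Rule B does not state, and Rule B is the only rule that names these professionals. A fuller protocol could not follow both sentences literally. The simplification is also disclosed with a reason, where most of these professionals work, that does not address what the public payer pays.

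Three stronger readings are tempting and are not supported.

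- **Wrong unit.** A reader might infer from counts of visits meeting an hourly rate that each visit is charged as a full hour. Nothing says so. Rate times duration is ordinary costing and is the method the article describes for ED costs, and a condensed article may leave the follow-up visit length to the full protocol.
- **A known direction.** A reader might infer that the physiotherapist arm is penalised. That needs both a private price above the public cost and more public visits in that arm; the documents give neither.
- **The ED physiotherapist.** Rule B also names the primary contact physiotherapist, but the point here is confined to consultations after discharge.

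**Conclusion.** The point holds as a conflict between two pricing rules for public-sector allied-health follow-up visits. If the private-rate rule is the one applied, those visits enter the Health system ICER at a price the public payer does not face.

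The size cannot be stated from the documents. It is nil when the price ratio is 1 or the arms use equal numbers of public visits. Otherwise it is proportional to the arm difference and to the excess of the price ratio over 1, and is divided by a QALY difference that may be small over three months. The illustrated range of 0 to 200 public visit costs per QALY rests wholly on assumed inputs. The effect reaches Objective 2 and the 0 to 3 month decision-tree costs that Objective 3 takes from the trial. The 3 to 24 month costs come from the literature and are not affected by this rule.

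It should be corrected before the cost analysis is run, because it bears on one of the two stated perspectives and is cheap to settle.

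**What to change.** 1. Price each recorded follow-up consultation by the sector the participant reported. Use the private fee for private visits. For public visits use a public unit cost that includes benefits and overhead; a private fee would normally cover overhead, so a bare wage could underprice public visits by comparison.
2. Extend the public-repository sentence to name public allied-health visits, and limit the private-rate sentence to private ones.
3. State the visit length assumed in the public unit cost, and vary that unit cost, including the length, in a sensitivity analysis.

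The cost is a change of wording, one extra unit-cost lookup and an assumed public visit length. The lookup is needed because the request to the hospital Finance Department (Study outcomes) covered ED management costs, not visits elsewhere after discharge. No new data collection should be needed, provided the questionnaires hold the public and private counts separately, as their description suggests; this should be confirmed first.

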### Study outcomes

Primary outcomes used to measure the average cost of an ED visit (Objective 1) will be the costs of care processes and the time associated with each care process. This method of costing is routinely used by some members of the research team [36, 45, 46]. The costs related to ED management (medical and non-medical staff, imaging, medication, consumables, maintenance, etc.) were obtained via a formal request made by a member of the research team to the CHU de Québec–UL Finance Department. The time associated with each care process was calculated by a member of the research team using estimates provided by the CHUL medical and non-medical staff that were validated during an observation period in the ED [36, 45]. Uncertainty in measured times will allow the variability of ED costs to be considered, and to derive a distribution of possible costs at baseline for each participant.

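### The rule that ED process time is the only source of variability conflicts, read literally, with the planned bootstrap and Monte Carlo analysis of costs; read narrowly, it leaves hourly rates without uncertainty or a sensitivity analysis

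*Protocol article*

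**What the plan says.** All references are to the protocol article.

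- **ED visit cost (Study outcomes, first paragraph).** Process times come from staff estimates that were checked during an observation period. "Uncertainty in measured times will allow the variability of ED costs to be considered", and this serves "to derive a distribution of possible costs at baseline for each participant".
- **Hourly rates (Study outcomes, second paragraph, which opens on Objectives 2 and 3).** Salary data from human resources for the professionals "considered will not allow for variability in hourly costs". The next sentence is the rule at issue: "The only source of variability considered for the purpose of these analyses will be that related to the time required for ED processes".
- **Source of the physiotherapist rate (same paragraph).** Rates for the primary contact physiotherapist and other non-physician professionals "will be derived from a search of the grey literature and will be based on rates in effect within the private healthcare system".
- **Follow-up costs (same paragraph).** Costs recorded by questionnaire at 1 and 3 months "will be added to the distribution of ED visit costs for each individual obtained under Objective 1".
- **Literature costs.** Study outcomes takes the 3 to 24 month costs from the literature. Data collection does the same for every parameter of the physiotherapist-alone model.
- **Uncertainty analysis (Data analysis and interpretation of results).** "Uncertainty in cost and effectiveness measures for the cost-utility analysis (Objective 2) will be obtained using non-parametric bootstrap resampling with replacement". For the model, "Uncertainty in the hybrid model parameters (probabilities, costs, and efficiency) (Objective 3) will be obtained via a probabilistic sensitivity analysis" by Monte Carlo simulation. Three scenarios follow: extreme 3-month utilities for missing participants, exclusion of outliers, and Markov states defined by pain interference.

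**The concern.** Two parts of the article describe cost uncertainty differently. One admits a single source, time spent on ED processes. The other resamples participants' costs and draws model costs from distributions. An analyst who follows the first would hold fixed several costs that are not ED process times at all.

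The treatment of hourly rates is a separate weakness that remains even if the sentence is meant narrowly. The reason given is that human-resources salary data show no spread. That does not fit a physiotherapist rate taken from a search of grey literature, where more than one value may be found and a range reported. Lack of an observed spread is not evidence that the rate is known exactly. The physiotherapist rate bears directly on the comparison, because physiotherapist involvement is what distinguishes the models of care.

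At stake is how much confidence the cost-effectiveness diagram, acceptability curve and frontier convey about which model is most efficient.

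**Working it through.** The article gives no cost standard deviation, interval or ICER, so there is no figure of its own to reproduce. The check has two parts.

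**1. Which cost components keep uncertainty under each reading**

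| Component | Source | Sentence read literally | Sentence limited to ED unit costing |
|---|---|---|---|
| ED process times | staff estimates, checked by observation | varies | varies |
| Follow-up resource use, 0 to 3 months | questionnaires | fixed | varies (bootstrap) |
| Costs from 3 to 24 months | literature | fixed | varies (Monte Carlo) |
| Physiotherapist-alone costs | literature | fixed | varies (Monte Carlo) |
| Hourly rates | public repositories, grey literature | fixed | fixed |

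The literal column cannot stand beside the data analysis section. The narrow column can, but its last row remains. A patient bootstrap cannot supply the missing rate uncertainty: one fixed rate applies to every resampled participant, so an error in it never enters the interval. The Gamma model for Objective 1 treats computed costs as data and has the same limit. None of the three scenarios changes a rate.

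**2. Illustrative size (every coefficient of variation, CV, and every share is assumed)**

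Mean total cost is scaled to 1. The article gives n = 78 but not the split by arm; 39 per arm assumes equal allocation, and about 31 per arm applies the 80% retention (0.8 × 39 = 31.2).

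- Patient-level standard error (SE) of the cost difference: SE = CV × √(2/n). With CV 1.0 and n = 39, SE = √(2/39) = 0.226.
- SE inflation when rates also vary: √(1 + (D × u / SE)²). D is the net between-arm cost exposed to uncertain rates, as a share of mean cost, and u is the CV of the rate.

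| D | u | D × u | Inflation at CV 1.0, n = 39 |
|---|---|---|---|
| 0.1 | 0.2 | 0.02 | 1.004 |
| 0.3 | 0.2 | 0.06 | 1.035 |
| 0.5 | 0.3 | 0.15 | 1.199 |

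Over the full assumed range (CV 0.5 to 1.5, D 0.1 to 0.5, u 0.1 to 0.3, n 31 or 39), the SE widens by 0% to 66%. The top value comes from CV 0.5, D 0.5, u 0.3 and n = 39: SE = 0.113 and √(1 + (0.15/0.113)²) = 1.66.

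If ED time were literally the only variability, and time variation were independent between participants (a further assumption), the SE relative to the patient-level SE would be (ED share of cost × time CV) / patient CV. With 0.6, 0.2 and 1.0 this is 0.12. The assumed extremes are 0.3 × 0.1 / 1.5 = 0.02 and 1.0 × 0.4 / 0.5 = 0.80. That loss comes from dropping the other cost variation, not mainly from fixing hourly rates.

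**The case against.** The best defence is context. The sentence directly follows the remark on salary data and agrees with the earlier statement that time uncertainty generates the ED cost distribution. It can therefore be read as explaining which ED costing input varies. Methods for uncertainty belong in the data analysis section, which assigns bootstrap and Monte Carlo explicitly. Treating public-repository prices as fixed in a base case is defensible, and the authors disclose the limit.

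Much of this stands. In particular, fixed hourly rates do not by themselves contradict a probabilistic analysis of costs, since costs can still vary through times, resource use and literature values. The conflict lies in the word *only*. The defence does not dispose of the paragraph's opening on Objectives 2 and 3, of the mismatch between the stated reason and the source of the physiotherapist rate, or of the absence of any rate scenario.

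Three stronger inferences are tempting but unsupported:

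- **That averaging participants' cost distributions makes a shared time error shrink with sample size.** This needs independent draws across participants. The article does not say how draws are made, and one shared draw per iteration is compatible with its text.
- **That hourly rates largely drive the difference between arms.** The article does not say so. Its introduction points to imaging, medication, consultations and repeat visits, which are resource use.
- **That the literature-based costs will in fact be held fixed.** The data analysis section includes model costs in the Monte Carlo analysis.

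**Conclusion.** The point holds as a conflict of wording with one substantive gap. Literally, the sentence and the data analysis section cannot both be followed, and the article does not say which governs. Under the narrower and more plausible reading, patient-level cost variation remains in the Objective 2 bootstrap, but hourly rates carry no uncertainty and no stated analysis tests them.

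The direction is clear: leaving out a real, independent source of cost uncertainty cannot widen the intervals. The size cannot be determined from the documents and may be small. A reader might infer that the intervals and acceptability curves are bound to be materially too narrow. That does not follow. It depends on which text governs and on cost shares that are not given, and the acceptability curves also carry QALY uncertainty, which a rule on cost variability need not remove. The percentages in the working are illustrations on assumed inputs, not estimates for this trial.

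**What to change.** 1. Limit the sentence in Study outcomes to the costing of the ED visit. This keeps the authors' disclosure about salary data and removes the conflict.
2. State in the data analysis section that follow-up costs, costs from 3 to 24 months and the literature-based costs of the physiotherapist-alone model receive distributions in the probabilistic analysis.
3. Vary the physiotherapist and physician hourly rates over the range found in the sources, both in the probabilistic analysis and in a one-way sensitivity analysis. Within an iteration, apply each drawn rate to all participants, because a rate error is common to them.

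The cost is a little more analysis work and possibly somewhat wider intervals. No new trial data are needed.
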